#### Health status

The EuroQol [33] is used to describe and evaluate health-related quality of life. Participants are requested (i) to rate their own health state of five dimensions (mobility, self-care, usual activities, pain/discomfort and anxiety/depression), (ii) to rate their current health status on a thermometer ranging 0-100 and (iii) to provide some background information on age, education, qualification, employment etc.

#### Health service costs

Costs of health and social care will be derived from data collected on each participant on inpatient/outpatient care, community and primary care services and the criminal justice system using the Economic Patient Questionnaire which includes a Psychiatric and a non-Psychiatric Hospital Record. The measure of patient outcome for the primary economic analysis will be quality adjusted life years (QALYs) gained at 2 years following recruitment to the trial. The QALYs will be estimated as the number of life years multiplied by the utility of each year of observed survival. The main framework of analysis will be cost effectiveness analysis and cost acceptability analysis.

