**Methods/Design:**

This is a single blind, intention-to-treat, multi-centre, randomized controlled trial comparing Cognitive Therapy for Command Hallucinations + Treatment as Usual with Treatment as Usual alone. Eligible participants have to fulfil the following inclusion criteria: i) ≥16 years; ii) ICD-10 diagnosis of schizophrenia or related disorder; iii) command hallucinations for at least 6 months leading to risk of harm to self or others. Following the completion of baseline assessments, eligible participants will be randomly allocated to either the Cognitive Therapy for Command Hallucinations + Treatment as Usual group or the Treatment as Usual group. Outcome will be assessed at 9 and 18 months post randomization with assessors blind to treatment allocation. The primary outcome is compliance behaviour and secondary outcomes include beliefs about voices' power, distress, psychotic symptoms together with a health economic evaluation. Qualitative interviews with services users will explore the acceptability of Cognitive Therapy for Command Hallucinations.

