## Method/Design

The trial is funded by the Medical Research Council and has received ethical approval from the West Midlands Research Ethics Committee.

This is a single (rater) blind, prospective, pragmatic randomised controlled trial, using intention to treat comparing CTCH + TAU with TAU alone. The trial is recruiting participants with schizophrenia and schizoaffective disorders, with treatment resistant auditory hallucinations from inpatient wards and community mental health teams in Birmingham & Leicester, London and Manchester. Recruitment to the trial began in February 2008 and was completed in July 2010. Follow-up assessments began in November 2008 and will be completed in January 2012.

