#### Planned Analyses

The evaluation of the primary outcome will be through an intention-to-treat (ITT) analysis using a logistic regression, allowing for centre membership and severity of command hallucinations at baseline. This will comprise a likelihood-based analysis to simultaneously estimate treatment effects at both the 9- and 18-month follow-up assessments and to allow for missing follow-up data that are assumed to be Missing at Random (MAR) in the terminology of Little & Rubin [36]. Analogous ANCOVA methods will be used for the analysis of the secondary outcomes.

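### The primary economic outcome is set at 2 years, but the stated follow-up schedule ends at 18 months

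*Protocol article*

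**What the plan says.** Health service costs in the Protocol article fixes the patient outcome of the primary economic analysis as "quality adjusted life years (QALYs) gained at 2 years following recruitment to the trial". The QALYs are to be formed as "the number of life years multiplied by the utility of each year of observed survival".

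Three other places describe follow-up:

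- Abstract, Methods/Design: "Outcome will be assessed at 9 and 18 months post randomization". The same paragraph lists the health economic evaluation with the secondary outcomes.
- Planned Analyses: the primary model is to "simultaneously estimate treatment effects at both the 9- and 18-month follow-up assessments", and secondary outcomes are handled analogously. The Secondary outcomes section counts costs among them.
- Method/Design: "Recruitment to the trial began in February 2008 and was completed in July 2010", and "Follow-up assessments began in November 2008 and will be completed in January 2012".

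Health status describes the EuroQol but gives no timetable for it. The article mentions no 24-month assessment and no modelling beyond 18 months.

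**The concern.** The horizon is part of what a QALY outcome means: it fixes the period over which health gain, and normally cost, is accumulated. Here the stated horizon is longer than the period the design is described as observing. An analyst following the text would have to supply the last six months by assumption, or shorten the horizon without authority from the text. The two routes can give different incremental QALYs. If the choice is left open until the economic data are seen, it can be influenced by the result. The reference to observed survival adds to the difficulty, because it suggests estimation within the trial rather than a model that runs past it.

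**Working it through.** **Inputs, all from the Protocol article**

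- QALY horizon: 2 years = 24 months from recruitment (Health service costs).
- Assessments: 9 and 18 months after randomisation (abstract; Planned Analyses).
- Recruitment: February 2008 to July 2010 (Method/Design).
- Follow-up: November 2008 to January 2012 (Method/Design).

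**Step 1. Do the dates match the assessment schedule?**

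- First recruit, first follow-up: February 2008 + 9 months = November 2008, the stated start of follow-up.
- Last recruit, last follow-up: July 2010 + 18 months = January 2012, the stated end of follow-up.

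The calendar reproduces the 9- and 18-month schedule exactly.

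**Step 2. Do the dates allow a 2-year horizon?**

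- Last recruit at 2 years: July 2010 + 24 months = July 2012, six months after follow-up closes.
- Latest recruitment month that reaches 2 years by the close: January 2012 − 24 months = January 2010.
- February 2008 to January 2010 is 24 of the 30 recruitment months. Those participants pass 2 years before the close, but no assessment is scheduled for them at that point.
- The remaining 6 recruitment months, February to July 2010, cannot reach 2 years within the stated follow-up.

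**Step 3. How much of the horizon has no scheduled assessment?**

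Assume that the EuroQol is taken at baseline, 9 and 18 months, with the rest of the battery.

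- Gap: 24 − 18 = 6 months; 6/24 = 25% of the horizon.
- Largest possible QALY total per participant, at a utility of 1 throughout: 1.5 over 18 months, against 2.0 over 24 months.

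**Step 4. How much can the missing period matter?**

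The article gives no expected utility difference, so this is an illustration on an assumed one: a between-arm gain that rises linearly from 0 to 0.05 at 9 months and holds at 0.05 to 18 months.

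- Months 0 to 9: 0.5 × 0.05 × 0.75 = 0.01875 QALY.
- Months 9 to 18: 0.05 × 0.75 = 0.0375 QALY.
- Total to 18 months: 0.01875 + 0.0375 = 0.05625 QALY.

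| Assumption for months 18 to 24 | Added QALY | Relative to 0.05625 |
|---|---|---|
| Gain lost at once | 0 | 0% |
| Gain fades linearly to zero | 0.5 × 0.05 × 0.5 = 0.0125 | +22% |
| Gain held | 0.05 × 0.5 = 0.025 | +44% |

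The percentages do not depend on the size of 0.05, which cancels. They do depend on the assumed shape over the first 18 months.

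**The case against.** The strongest defence is that this is a condensed article. The full protocol or a health-economic plan may schedule a later EuroQol or describe an extrapolation, and detail left to those documents is no fault here. That is right for omitted detail, but the article states both a horizon and a schedule, and the two do not agree. The published text needs reconciling whatever the fuller plan says.

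A second defence is that the 2 years run from recruitment and the 18 months from randomisation. Under Recruitment and randomisation, allocation follows completion of the baseline battery, and nothing suggests a six-month interval. The dates in Method/Design run from recruitment and still give 18 months.

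Several stronger readings are tempting, and the article does not support them:

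- **That the last six months have no data for any participant.** This can be said only of scheduled assessments. The cost questionnaire includes hospital records, and such records or survival status could exist beyond 18 months for earlier recruits, although the article plans no such collection.
- **That the utility schedule is a stated fact.** It is inferred from the general schedule.
- **That the QALY formula fails because no utility is measured at year boundaries.** The formula reads as a general description of a QALY. Values at 0, 9 and 18 months can be interpolated, and how to do so is detail for the full plan.
- **That the cost per QALY must be distorted.** No cost window is stated. Carrying both costs and effects to 24 months need not bias the ratio, and if 2 years is a slip for 18 months nothing is distorted. The illustration concerns QALYs only.

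**Conclusion.** The point holds as an internal contradiction. The primary economic outcome is defined over 24 months, while the stated schedule and calendar support 18. On the assumption that the EuroQol follows the general schedule, 25% of the horizon has no scheduled utility assessment, and the 2-year QALY depends on an extrapolation that the article does not mention. In the illustration, the choice of extrapolation moves the incremental QALY by 0% to +44%. That range shows that the choice can matter; it does not predict this trial's result.

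The scope is limited to the economic evaluation, which is secondary in the trial. The primary outcome on the Voice Compliance Scale, its analysis and the sample size are untouched. This is a should-fix.

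**What to change.** Under Health service costs, restate the primary economic horizon as 18 months after randomisation, for both costs and QALYs. Define QALYs as the area under the EuroQol utility curve through baseline, 9 and 18 months; by the trapezium rule, for a participant alive throughout, 0.75 × (u0 + u9)/2 + 0.75 × (u9 + u18)/2. Label any 24-month figure as a modelled scenario and state its assumptions about months 18 to 24 for costs as well as utilities. If the fuller plan does contain a 24-month collection or an extrapolation method, the article should say so instead. Either way, settle the horizon before the economic results are seen.

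The 18-month version needs only a change of wording and uses data collected under the existing schedule, which was still running when the article was written. The small downside is a shorter horizon: any benefit or cost after 18 months moves from the primary economic result to the modelled scenario.

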### Primary Outcome

Primary outcome is compliance behaviour assessed using the Voice Compliance Scale (VCS) [13,14].

### Secondary outcomes

Secondary outcomes include beliefs about voices' power, distress, symptoms and costs. The acceptability of CTCH and user views about the active ingredients is explored through semi-structured interviews with a purposeful sample of users at the end of the intervention. The interview schedule will be piloted and modified as necessary. In all cases, interviews will be audio taped and fully transcribed. Interviews and analysis will be carried out concurrently and interviews will continue until data saturation is complete (approximately 10 users in each site). Data from semi-structured interviews will be analysed using a grounded theory approach [34] where theories are generated from data; this will follow the methodology of a recent study conducted by one of the applicants [35].

### Predictor variables

History of suicide, self harm and harm to others is collected as part of the baseline assessments. Data about childhood trauma and abuse is also routinely collected using the Childhood Trauma Questionnaire.

### Analysis

#### Power

A sample size of 100 per group will have 84% power to detect an absolute difference between a proportion who have acted on their voices of 40% under TAU and 20% under the CTCH arms using a Pearson chi-square test with two-tailed significance level of 0.05.

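### The stated 84% power does not belong to the Pearson chi-square test with 100 observed per arm, which gives 87.6%; the sentence should say what the 84% refers to

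*Protocol article*

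**What the plan says.** In the protocol article, the Power paragraph under Analysis gives the whole sample size calculation in one sentence. The size and power are "A sample size of 100 per group will have 84% power to detect an absolute difference". The effect is "a proportion who have acted on their voices of 40% under TAU and 20% under the CTCH arms". The method is "using a Pearson chi-square test with two-tailed significance level of 0.05". The sentence mentions neither a continuity correction nor an allowance for loss to follow-up, and does not say whether 100 per group counts people randomised or people analysed.

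The next paragraph, Planned Analyses, specifies a logistic regression adjusted for centre and baseline severity. It is fitted by likelihood to the 9- and 18-month assessments together, and incomplete follow-up is handled under a missing-at-random assumption. So some missing outcomes are expected, but no rate is given.

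**The concern.** A reader who puts the printed inputs into the named test does not get the printed power. Since test, significance level, proportions and group size are all stated, this is an inconsistency within the text and not a detail left out for brevity.

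What is at stake is how the figure is read. Power is the main planning figure and the benchmark against which a null result will be judged. The 84% could describe a more conservative test on complete data, or the named test after some loss. These readings imply different power once outcomes are missing, and the article gives no means of telling them apart.

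**Working it through.** **Inputs**, all from the Power paragraph: n = 100 per arm, p1 = 0.40, p2 = 0.20, difference 0.20, mean proportion 0.30, two-sided 0.05 (z = 1.96).

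**Step 1. The named test (uncorrected Pearson, pooled variance under the null).**

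Power = Φ{[d − 1.96·√(2·p̄(1−p̄)/n)] / √(p1(1−p1)/n + p2(1−p2)/n)}

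- Null standard error: √(2 × 0.3 × 0.7/100) = √0.0042 = 0.0648, and × 1.96 = 0.1270
- Alternative standard error: √(0.24/100 + 0.16/100) = √0.004 = 0.0632
- (0.20 − 0.1270)/0.0632 = 1.154, so power = **87.6%**
- Exact binomial enumeration of the same test: **88.0%**

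The gap to the printed 84% is 3.6 points, too large for rounding.

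**Step 2. Which calculation gives 84% with 100 per arm?**

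Subtracting the continuity correction 1/n = 0.01 from the difference:

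- (0.20 − 0.01 − 0.1270)/0.0632 = 0.996, so power = **84.0%**
- Enumeration with the Yates correction: 84.4%; Fisher's exact test: 84.4%
- Solving the continuity-corrected formula for 84% power returns exactly 100 per arm

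Other common variants at 100 per arm do not give 84%: unpooled variance 88.5%, arcsine 87.8%, one-sided test 93.0%.

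**Step 3. Which number gives 84% under the named test?**

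The Step 1 formula with fewer observed:

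- n = 90: (0.20 − 1.96·√(0.42/90))/√(0.40/90) = 0.992, power 83.9%
- n = 91: the same formula gives 1.008, power 84.3%

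So 84% is also the Pearson power if about 9 to 10 of every 100 per arm have no outcome.

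**Step 4. How far the readings diverge under loss.** The article gives no loss rate. The rates below are assumptions, shown only as a range.

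| Assumed loss | Observed per arm | Pearson | Continuity-corrected |
|---|---|---|---|
| 0% | 100 | 87.6% | 84.0% |
| 5% | 95 | 85.9% | 81.9% |
| 10% | 90 | 83.9% | 79.5% |
| 15% | 85 | 81.8% | 76.9% |
| 20% | 80 | 79.4% | 74.0% |

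These describe a two-group comparison at one time point among those observed. They are not the power of the planned model, which uses both follow-ups and a baseline covariate.

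**The case against.** The strongest reply is that the figure does reproduce. A continuity correction is an adjustment to the same Pearson statistic, and with it the calculation gives 84.0% and exactly 100 per arm. On that view the sentence lacks a qualifier and no more. The error is also on the safe side, since the named test with complete data has more power than claimed. Recruitment was completed in July 2010 according to Method/Design, so no design decision turns on it.

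Most of this stands, and it limits the weight of the point. It does not remove it: the correction is not mentioned, and an allowance for loss explains the figure equally well.

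A reader might go further and infer that 84% leaves no room for loss to follow-up, or that the trial is underpowered. The documents do not support that. It would follow only if 84% were known to be the continuity-corrected figure on 100 observed per arm. Under the named test, 84% already accommodates about 9 to 10% loss, and power is still 79.4% at an assumed 20% loss. The absence of a loss rate is not itself a fault, because a condensed article may leave it to the full protocol, and Planned Analyses does address missing follow-up. Nor is there an error in planning a logistic regression with a two-proportion calculation; asking for power from the longitudinal model would be a preference.

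**Conclusion.** The point holds as an inconsistency between the printed test, power and number. On the article's own inputs the Pearson chi-square has 87.6% power (exact 88.0%), not 84%. The 84% corresponds either to the continuity-corrected test with 100 observed per arm or to the Pearson test with about 90 to 91, and the article does not show which. For the named test with complete data the printed figure understates power by 3.6 points, so nothing here says that the sample is too small. The arithmetic rests only on stated inputs and equal groups; the figures under loss rest on assumed rates. This is a correction to the reporting of a planning figure, and no planned analysis is affected.

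**What to change.** Amend the one sentence in the Power paragraph so that test, power and number agree, according to what was actually done:

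- state 87.6% power for the Pearson chi-square test with 100 evaluable per arm; or
- keep 84% and say that the chi-square test is continuity-corrected, with 100 evaluable per arm; or
- keep 84% for the Pearson test and state the allowance of roughly 9 to 10% loss that it implies, i.e. about 90 to 91 observed per arm.

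In each case say whether 100 per group are randomised or analysed. If power under other loss rates is shown, label it as an assumed range, for example Pearson 81.8% at 15% loss and 79.4% at 20%.

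The cost is one reworded sentence. The sample size and the analysis stay as they are.

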#### Planned Analyses

The evaluation of the primary outcome will be through an intention-to-treat (ITT) analysis using a logistic regression, allowing for centre membership and severity of command hallucinations at baseline. This will comprise a likelihood-based analysis to simultaneously estimate treatment effects at both the 9- and 18-month follow-up assessments and to allow for missing follow-up data that are assumed to be Missing at Random (MAR) in the terminology of Little & Rubin [36]. Analogous ANCOVA methods will be used for the analysis of the secondary outcomes.

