### Hypotheses

The primary hypothesis to be tested is whether in patients with command hallucinations who have acted on their voices and are therefore at high risk of doing so again, cognitive therapy for command hallucinations (CTCH) will prevent further harmful compliance behaviour, and thereby reduce risk.

Secondary hypotheses predict that:

(a) any reduction in compliance will be mediated by reduced conviction in the perceived power of the persecuting voice,

(b) CTCH will reduce delusional distress and depression, but

(c) we are not predicting any change in the frequency or topography of voices per se.

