### Inclusion and exclusion criteria

Eligible participants fulfil the following criteria: i) ICD-10 schizophrenia, schizoaffective (F20,22,23,25,28,29: WHO, 1999) [21], or ICD-10 diagnosis of Mood disorders (F32) under care of the clinical team (ii) age ≥16, (iii) history of command hallucinations of at least 6 months with history of harm to self, others or major social transgressions as a result of the commands; or harmful command hallucinations where the individual is distressed and appeasing the powerful voice. Exclusion criteria include: organic impairment or addictive disorder considered to be the primary diagnosis and insufficient command of the English language.

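### The primary logistic model names centre and an undefined baseline severity but not baseline compliance, although eligibility mixes past compliers with people who only appease; adjusting for it would cost almost nothing

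*Protocol article*

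**What the plan says.** - **Primary model** (Protocol article, Planned Analyses): an intention-to-treat logistic regression, "allowing for centre membership and severity of command hallucinations at baseline", estimating effects at 9 and 18 months together. No scale is given for severity.
- **Primary outcome** (Primary Outcome; Behavioural responses to voices): compliance on the VCS. Appeasement scores 2 or 3; partial or full compliance with a severe command scores 4 or 5.
- **Hypothesis** (Hypotheses): it concerns "patients with command hallucinations who have acted on their voices and are therefore at high risk of doing so again", and asks whether therapy prevents further harmful compliance.
- **Eligibility** (Inclusion and exclusion criteria): one route requires past harm or major social transgression resulting from commands. The other route is "or harmful command hallucinations where the individual is distressed and appeasing the powerful voice", with no past harmful act required.
- **Allocation** (Recruitment and randomisation): stratified by centre only, after a battery of baseline assessments.
- **Other baseline data** (Predictor variables): "History of suicide, self harm and harm to others is collected as part of the baseline assessments".
- **Sample size** (Power): "A sample size of 100 per group will have 84% power". The planning rates are "a proportion who have acted on their voices of 40% under TAU and 20% under the CTCH arms"; the test is an unadjusted Pearson chi-square, two-sided at 0.05.

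**The concern.** Two separate matters meet here.

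**The covariate.** The two entry routes correspond to different levels of the primary outcome scale, and the hypothesis itself reasons from past action to future risk. A baseline measure of compliance is therefore an obvious candidate for the model. It is neither a stratification factor nor a named covariate. A chance difference between arms in the share of past compliers would then go uncorrected in the primary estimate, and some precision would be given up.

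**The population.** A hypothesis about further compliance in people who have already complied is not the same as a comparison in a sample that also contains people who have only appeased. The reader cannot tell which group the result is meant to describe, nor which group the planning rate of 40% comes from.

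**Working it through.** **1. The protocol's own figure.** Inputs from the Power section: n = 100 per arm, 40% versus 20%, two-sided 0.05.

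Power = Φ[(d − c − 1.96·SE0)/SE1], where SE0 = √(2p̄(1−p̄)/n), SE1 = √(p1(1−p1)/n + p2(1−p2)/n), and c = 0 without or 1/n with a continuity correction.

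- d = 0.20, p̄ = 0.30, SE0 = 0.0648, SE1 = 0.0632.
- Uncorrected: (0.20 − 0.1270)/0.0632 = 1.154, power 87.6%.
- Corrected: (0.19 − 0.1270)/0.0632 = 0.996, power 84.0%.

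The stated 84% reproduces with the continuity correction. It assumes no covariate.

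**2. What a baseline stratum would add.** The documents give neither the share of appeasers nor rates by stratum, so these are assumptions. Trials of 100 per arm were simulated with overall rates held at 40% and 20%, a binary stratum (past complier or appeaser only), and likelihood-ratio tests from logistic models with and without the stratum (5,000 trials per row; simulation error about 0.5 point).

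| Appeasers | TAU rate, compliers / appeasers | Without stratum | With stratum |
|---|---|---|---|
| 20% | 42% / 32% | 88.4% | 88.6% |
| 20% | 48% / 8% | 88.1% | 90.0% |
| 35% | 43% / 33% | 87.8% | 88.3% |
| 35% | 54% / 14% | 88.7% | 91.7% |
| 50% | 45% / 35% | 89.1% | 89.0% |
| 50% | 60% / 20% | 88.0% | 91.5% |

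The gain is about 0 to 3.5 points for gaps of 10 to 40 points between strata. At a gap of 50 points the same method (4,000 trials) gives about 5: 88.2% to 93.0% with 35% appeasers (57.5% / 7.5%), and 87.7% to 93.4% with 50% (65% / 15%). The simulation uses one time point and omits centre and severity. If severity carries part of the same information, the gain is smaller.

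**3. Chance imbalance.** Take 35% appeasers and TAU rates of 54% and 14%. The difference between arms in the share of appeasers has SD √(2 × 0.35 × 0.65/100) = 0.067. An imbalance of 1.96 SD is 13.2 points. Multiplied by the 40-point gap, this shifts the unadjusted risk difference by 0.132 × 0.40 = 5.3 points. Under treatment the gap is narrower: the conditional odds ratio of 0.331 in this scenario gives 28.0% and 5.1%, a gap of 22.9 points. With the mean of the two gaps, 31.4 points, the shift is 4.2 points. So an unlucky allocation moves the estimate by about 4 to 5 points, against a planned difference of 20.

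**4. If 40% describes past compliers only.** Suppose a share f are appeasers with TAU rate q, and the relative halving holds in everyone. TAU = (1−f) × 0.40 + f × q, and CTCH = TAU/2.

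- f = 0.2, q = 0.10: 0.34 versus 0.17. Power is 79.2% uncorrected, 74.2% corrected.
- f = 0.2, q = 0.20: 0.36 versus 0.18. Power is 82.3% uncorrected, 77.7% corrected.
- f = 0.5, q = 0.10 to 0.30: 62.1% to 80.8% uncorrected.

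The reference values are 87.6% and 84.0%. This loss comes from the smaller absolute difference, so adjustment would not remove it.

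**The case against.** The strongest reply is that nothing is broken. Randomisation makes the comparison valid without the covariate. The 84% is for an unadjusted chi-square test, so a reader who infers that the planned power is lost through the model is mistaken: only a possible gain is forgone. That stands.

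Severity is also undefined, so it might mean or include the VCS, and a fuller plan may say so. That stands too. It limits the size of the point, but the covariate list in the article is still one that does not name baseline compliance.

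Three further inferences are tempting and not supported:
- **That appeasers must pull the control rate below 40%.** The Power section does not say whose rate 40% is; it may already describe the eligible mix.
- **That past compliance is the strongest predictor available.** The Hypotheses section links it to risk but does not rank it. The Background gives weight to thoughts about violence, beliefs about having to obey, and perceived voice power.
- **That past compliance with commands is already recorded under Predictor variables.** That section lists a history of suicide, self-harm and harm to others, not harm in response to commands. A baseline VCS very probably exists, since the assessments precede allocation, but the article does not say so outright.

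On the population, the Discussion does mention people at high risk of acting as well as those who act. This suggests that the wider group was intended, but it leaves the narrower wording of the primary hypothesis in place.

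**Conclusion.** The point holds as an inexpensive improvement to the primary model, not as a flaw that invalidates it. The forgone gain is about 0 to 5 points of power at 100 per arm. An unlucky imbalance could shift the unadjusted estimate by about 4 to 5 points in one of the stronger scenarios. Both sizes rest on assumed shares and stratum rates, and both shrink if severity already reflects compliance.

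The mismatch between hypothesis and eligibility is certain from the text, but it is a matter of wording and interpretation that the model neither causes nor cures. Its effect on power is conditional: it arises only if 40% was meant for past compliers, and then amounts, for example, to 74-78% instead of 84% with 20% appeasers at a 10-20% control rate.

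**What to change.** Before unblinded analysis:

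1. Name the instrument behind baseline severity.
2. Add the pre-randomisation VCS level to the primary model, alongside centre and severity. If no baseline VCS was recorded, use the entry route (past harmful compliance or appeasement only), taken from the eligibility screen if it is held there.
3. Reconcile the population in the primary hypothesis with the eligibility criteria, and state which population the 40% TAU rate describes. If it is past compliers only, give the power for the mixed sample.

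The cost is one or two degrees of freedom and a few sentences. No new data should be needed if the baseline VCS or entry route is on file. Recruitment is complete, but follow-up runs to January 2012, so the wording can still be settled in time. The adjusted odds ratio becomes conditional on the added covariate: in the scenarios above it is about 0.32 to 0.37, against an unadjusted (0.20/0.80)/(0.40/0.60) = 0.375. The report should say which is quoted.

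Reporting the effect separately in past compliers, or testing an interaction, is optional; with 200 patients it would be supportive only.
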